### Support

The participants will be supported by trained coaches according to a manual written by the first author. The support will consist of the general availability of the coach to answer any questions that might occur, reminders sent by the coach when a patient has not completed a module in seven days, and brief feedback provided by the coach on completed online exercises (within the module) and on the completion of the homework assignments. The coach will write the feedbacks via a messaging system on the training homepage after the respective participant will have finished a module.

The total amount of time spent on each participant will be about three hours for the total duration of the intervention. The coaches will be supervised (first author).

### Experimental condition

Participants in the intervention group will receive GET.ON Recovery after randomization. Participants in the control group receive GET.ON Recovery six months after randomization. Subjects of the control group will not be supported with feedback or reminders, but the primary study investigator will be available for questions concerning the content of the intervention or for technical problems.

### Instruments

Table 
1 provides an overview of the applied instruments at each point in time. We expect participants to need approximately 30 minutes to complete the questionnaires at one point in time.

**Table 1 T1:** Overview of instruments per time of measurement (T0, T1, T2)

	**Number of items**	**Screening**	**T0**	**T1**	**T2**
			**(baseline)**	**(8 weeks)**	**(6 months)**
Socio-demographic data	20	x	-	-	-
Insomnia severity (ISI)	7	x	x	x	x
Work stress (IS, Subscale CI)	3	x	x	x	x
Sleep effort (GSES)	7	-	x	x	x
Sleep diary	10	-	x	x	-
Adherence to sleep hygiene (SHI)	13	-	x	x	x
Recuperation in sleep (items of SF-B)	7	-	x	x	x
Sleep quality (item of PSQI)	1	-	x	x	x
Effort reward imbalance (ERI-S)	10	-	x	-	-
Depressive symptoms (ADS)	20	-	x	x	x
Worrying (PSWQ-PW, ultra short)	3	-	x	x	x
Recovery experiences (REQ)	16	-	x	x	x
Recovery activities (ReaQ)	21	-	x	x	x
Quality of life (SF-12)	12	-	x	x	x
Presenteeism, absenteeism and health care utilization (TicP)	Depends	-	x	-	x
Teacher self-efficacy (Teacher self-efficacy scale)	10	-	-	-	x
Work engagement (UWES)	9	-	x	-	-
User satisfaction	8	-	-	x	-

*ADS* Allgemeine Depressionsskala, *CI* Cognitive Irritation, *ERI-S* effort-reward imbalance – short version, *GSES* Glasgow Sleep Effort Scale, *IS* Irritation Scale, *PSQI* Pittsburgh Sleep Quality Index, *PSWQ-PW* Penn State Worry Questionnaire – Past Week, *ReaQ* Recovery experience and activities questionnaire, *REQ* Recovery Experience Questionnaire, *SF-12* Short Form Health Survey – 12 items, *SF-B* Schlaffragebogen B, *SHI* Sleep Hygiene Index, *TicP* Trimbos/iMTA questionnaire for costs associated with Psychiatric illness, *UWES* Utrecht Work Engagement Scale.

#### Screening

The ISI
[44], the ‘Cognitive Irritation’ subscale of the IS
[45], and item 9 of the BDI II
[46] will be administered as screening measures.

#### Primary outcome measure

The primary outcome measure is insomnia severity (ISI).

#### Secondary outcome measures

**Demographics** A self-designed questionnaire will be used to collect participants’ demographic data, such as living situation, type of school they work in and age.

##### Sleep effort

We will measure sleep effort with the Glasgow Sleep Effort Scale (GSES). This 7-item scale (for example, ‘I put too much effort into sleeping when it should come naturally’) is answered on a 3-point Likert scale (very much, to some extent, not at all). The scale has been validated with a reported internal consistency of .77
[58].

##### Sleep diary

Participants will complete an online sleep diary for seven days, both at T0 and T1. In the diary, participants will record the time at which they leave their bed each morning, their previous evening bedtime and the total hours of sleep. Sleep efficiency (SE) and total sleep time (TST) will be computed as outcome measures from the diary data. Additionally, the diary will also contain data, such as information regarding sleep quality, worrying before going to bed, sleep effort and recreational activities in the previous day. Participants will be encouraged to use this diary also in the course of the intervention.

##### Sleep hygiene

The Sleep Hygiene Index
[59] is a validated instrument comprising 13 items that assess the frequency of sleep-impaired behaviors during the previous 14 days (for example, ‘I think, plan, or worry when I am in bed’) and a 5-point Likert scale (0 = never; 4 = always). We will recode the sum score so that higher scores indicate a better sleep hygiene.

##### Recuperation in sleep

Recuperation in sleep can be assessed by two items from a well-validated questionnaire
[60] that has been recommended as an outcome measure by the German Society of Sleep Medicine (DGSM). Participants rate a) if they needed some extra time to ‘get going’ in the morning and b) how they felt after awakening during the previous 14 days according to seven feelings (for example, tired, relaxed). Both items are answered on a 5-point Likert scale (never, almost never, sometimes, often, always).

##### Sleep quality

We will assess sleep quality with one single item derived from the Pittsburgh Sleep Quality Index (PSQI)
[61]. The answer is given on a 4-point Likert scale (‘How do you evaluate the quality of this week’s sleep?’ 1 = very good; 4 = very poor). We will recode the item so that higher scores indicate better sleep quality.

##### Work stress

We will assess work stress with a validated 10-item short version of the Effort-Reward-Imbalance questionnaire (ERI-S)
[62]. All items (for example, ‘Considering all my efforts and achievements, I receive the respect and prestige I deserve at work’) are answered on a 4-point Likert scale (1 = strongly agree; 4 = strongly disagree). By using the two subscales, ‘effort’ and ‘reward’, a score for ‘effort-reward imbalance’ can be computed. The ERI-S is a well-established measure for work stress, and its psychometric quality is satisfactory to good
[62].

##### Depressive symptoms

The Allgemeine Depressions-Skala (ADS)
[63] is the German adaptation of the Centre for Epidemiological Studies Depression Scale (CES-D) developed at the National Institute for Mental Health. It is a frequently and commonly used self-report instrument measuring depressive symptoms in the week preceding the assessment. The ADS consists of 20 items answered on a 4-point Likert scale. The total score ranges between 0 and 60. Internal consistency is reported to be α = .89, split-half reliability is *r* = .91
[63].

##### Worrying

We will use a 3-item short version of the Penn State Worry Questionnaire (PSWQ)
[64,65] and adapt it as a past-week version according to the respective three German items of the Penn State Worry Questionnaire-Past Week (PSWQ, PW
[66]. The questionnaire assesses pathological worry during the past week and is answered on a 7-point Likert scale. Internal consistency of the English ultra-brief version of the PSWQ is reported to be α = .85, which is comparable to the internal consistency of the English PSWQ and the German PSWQ-PW version.

##### Work-related rumination

In conformance with Berset
[23], we will measure work-related rumination with the ‘Cognitive Irritation’ subscale of the Irritation Scale (IS,
[45]. Internal consistency is reported to be α = .86. A score of 15 or higher indicates an above-average level of rumination (Stanine ≥7)
[45].

##### Recovery experiences

The recovery experience questionnaire (REQ
[67], is a validated 16-item measure answered on a 5-point Likert scale that assesses recuperation and unwinding from work. The items load on four factors that represent four different recovery experiences: psychological detachment (α = .85), relaxation (α = .85), mastery (α = .85) and control (α = .85). A sum score can be computed for each scale.

##### Recovery activities

The Recreation experience and activity Questionnaire, (ReaQ) by [name] (DL, paper submitted) comprises 21 items that assess the frequency of several recreational activities during the past week. Answer categories include ‘never’, ‘one time’, ‘two times’, ‘three times’ or ‘at least 4 times’. Internal consistency of the questionnaire is α = .83.

##### Teacher self-efficacy

Self-efficacy will be measured by the Teacher Self-Efficacy Scale
[68], a 10-item self-rating instrument that has been shown to have good reliability and validity and to have potential for predicting work-related stress symptoms
[69].

##### Work engagement

Work engagement is assessed by the Utrecht Work Engagement Scale (UWES, German version)
[70]. Its 17 items represent three subscales: vigor, dedication and absorption. Internal consistency is α = .91 for the total score.

##### User satisfaction

We will assess user satisfaction by a self-designed questionnaire based on the ‘Satisfaction with Psychotherapy’ Questionnaire (ZUF-8)
[71] and the German version of the Client Satisfaction Questionnaire (CSQ-8)
[72]. We will also assess satisfaction before the beginning of each module by asking participants how useful and helpful the information from the previous module appeared to them.

##### Quality of life

Improvement of health-related quality of life (HRQL) is measured by the well-established short version (SF-12)
[73] of the Short Form 36 Health Survey Questionnaire (SF-36)
[73]. This self-report measure is a generic, 12-item, multi-purpose health survey, with eight scales (Physical Functioning, Role-Physical, Bodily Pain, General Health, Vitality, Social Functioning, Role-Emotional, Mental Health) and two summary measures indicating quality of life with regard to mental health and quality of life with regard to physical health. Most of the items are answered on a 3-, 5- or 6-point Likert scale.

#### Economic evaluation

**Quality-adjusted life years (QALYs)** QALYs will be obtained from the SF-6D
[73]. The SF-6D contains six dimensions (each with between 2 and 5 levels) and includes 7 items of the SF-12. The SF-6D generates 7500 different health states. Utility values will be derived using Brazier’s algorithm
[74,75].

##### Presenteeism, absenteeism and health care utilization

We adapted the Trimbos/iMTA questionnaire for costs associated with Psychiatric Illness (TiC-P)
[76] due to insomnia and occupational stress in German teachers.

### Statistical analysis

The analyses will be conducted according to the CONSORT guidelines. All analyses will be based on the intention-to-treat sample. Missing values will be imputed by state of the art imputation methods.

#### Treatment efficacy

We will perform repeated measures ANOVAs to compare the intervention group and the waitlist control group on the primary and secondary outcome measures. Cohen’s d will be used for the between group effect size, calculated
[77]. Apart from statistical significance tests, we will also look at the clinical significance of our data by detecting reliable changes and recovery rates using the method of Jacobson and Truax
[78].

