**Methods/Design:**

In a two-arm randomized controlled trial (N = 128), the effects of a guided online sleep training will be compared to a waitlist-control condition. German teachers with significant clinical insomnia complaints (Insomnia Severity Index ≥15) and work-related rumination (Irritation Scale, subscale Cognitive Irritation ≥15) will be included in the study. The primary outcome measure will be insomnia severity. Additionally, an economic evaluation from a societal perspective will be conducted. Data from the intention-to-treat sample will be analyzed two and six months after randomization.

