### Randomization

A computer program will automatically assign a 0 or 1 to each ID number, indicating the allocation to either the intervention or a waiting list. This random assignment is made in a 1:1 ratio.

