### Sample size

The sample size will be based on the difference between experimental and control group at post-test on the primary outcome measure (insomnia severity). We expect a difference of Cohen’s d = .50. Given an alpha of .05 and 1 - beta = .80 in a two-tailed test, we will need 64 subjects in each condition with a total sample size of N = 128. Based on a recent meta-analysis on the efficacy of online insomnia trials
[33], we could expect a higher effect size (d = .86) for our primary outcome. But our target group differs from the group assessed in the meta-analysis, thus we chose a rather conservative estimate to reduce the chance of an under-powered study.

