#### Diary data

Sleep efficiency (SE) and total sleep time (TST) will be recorded in a sleep diary at pre- (T0) and post-treatment (T1), seven times in the course of seven days. We will compare SE and TST means in a repeated-measures ANOVA to evaluate treatment efficacy (see above). Diary data participants collect over the course of the intervention will be explored using multilevel modeling procedures.

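### The sample size rests on the group difference in ISI at post-test (T1), but the repeated-measures ANOVA named for efficacy is not tied to that contrast and states no baseline adjustment

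*Protocol article*

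**What the plan says.** Under Sample size, the article fixes the contrast of interest: "The sample size will be based on the difference between experimental and control group at post-test on the primary outcome measure (insomnia severity"). The inputs are "We expect a difference of Cohen’s d = .50" and "Given an alpha of .05 and 1 - beta = .80 in a two-tailed test", with the result that "we will need 64 subjects in each condition with a total sample size of N = 128".

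Under Treatment efficacy, the method is different: "We will perform repeated measures ANOVAs to compare the intervention group and the waitlist control group on the primary and secondary outcome measures". The text does not say which time points enter, which term is the test, or whether baseline is a covariate. Under Diary data, the same method is carried over to sleep efficiency and total sleep time: "We will compare SE and TST means in a repeated-measures ANOVA to evaluate treatment efficacy (see above").

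No other section ties the primary analysis to T1. The primary outcome section names the ISI without a time point. Table 1 has the ISI at T0, T1 and T2. The abstract states: "Data from the intention-to-treat sample will be analyzed two and six months after randomization".

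**The concern.** The trial was sized for one question: do the arms differ in ISI at eight weeks? The named analysis can answer a different one. With three time points the usual efficacy term, group x time, asks whether the difference between arms varies anywhere over T0, T1 and T2. A significant result would not show a difference at T1, and its power depends on the six-month effect, which the sample size calculation does not consider. With two time points the term does target the T1 effect, but as a difference in change scores. That makes weaker use of T0 ISI than entering it as a covariate.

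At stake are the meaning of the primary P value and, in some plausible settings, a material share of the power.

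**Working it through.** **Inputs from the article.** d = .50 at T1, two-sided alpha .05, power .80, 64 per arm (Sample size); 1:1 allocation (Randomization).

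**Assumed, because the article gives no values.** r = correlation of T0 with T1 ISI; k = SD at T0 divided by SD at T1; the effect at T2; complete data.

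**Step 1: the plan's own figure.** Two-sample t-test with noncentrality d x sqrt(n/2). For n = 64 this is .50 x sqrt(32) = 2.83 on 126 df, giving power .801; n = 63 gives .795. So 64 per arm is exact for an unadjusted comparison at T1.

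**Step 2: T0 and T1 only.** The group x time term is the t-test on change. In units of T1 variance:

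- change score: 1 + k² - 2rk
- ANCOVA: 1 - r²
- difference: k² - 2rk + r² = (k - r)², which is never negative

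Dividing .50 by the square root of each variance gives the effective d, and the noncentral t gives the power (126 df for change, 125 for ANCOVA):

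| k | r | Change variance | ANCOVA variance | Power, T0-T1 interaction | Power, ANCOVA |
|---|---|---|---|---|---|
| 1 | .3 | 1.40 | .91 | 66.0% | 83.7% |
| .8 | .3 | 1.16 | .91 | 74.1% | 83.7% |
| .6 | .3 | 1.00 | .91 | 80.1% | 83.7% |
| 1 | .5 | 1.00 | .75 | 80.1% | 90.0% |
| .6 | .5 | .76 | .75 | 89.6% | 90.0% |

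The interaction falls below the planned power only when its variance exceeds 1, that is when k² > 2rk, or r < k/2. ANCOVA variance never exceeds 1.

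**Step 3: T0, T1 and T2.** Group x time has 2 and 252 df. Under compound symmetry with k = 1, the noncentrality is (n/2) x S/(1 - r), where S is the sum of squared deviations of the three group differences from their mean.

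| Group difference at T0, T1, T2 | S | Power, r = .3 | Power, r = .5 |
|---|---|---|---|
| 0, .50, .30 | .127 | 56% | 72% |
| 0, .50, .50 | .167 | 69% | 84% |
| 0, 0, .50 | .167 | 69% | 84% |

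The last two rows have the same S. The omnibus term therefore rejects as often when there is no T1 effect and d = .50 at T2 as when d = .50 is present at both.

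**The case against.** The strongest reply has three parts. First, this is a condensed article, and the tested term, time points and covariates are commonly set out in a full analysis plan. Second, under randomisation the T0-T1 interaction estimates the T1 effect without bias and with correct type I error, so preferring ANCOVA is a gain in efficiency and not the repair of an error. Third, d = .50 was chosen as conservative against the .86 of the cited meta-analysis; at d = .86 even k = 1, r = .3 gives the interaction about 98% power.

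The second part stands fully, and the third stands if the effect is that large. The first stands only in part: the article does name its method, and that method does not by itself deliver the contrast used for the sample size.

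A reader might also infer more than the document supports:

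- **That power under the planned test is simply not .80.** It is at or above .80 whenever r is at least k/2 for the two-time interaction, and it is 84% for the three-time interaction with a sustained effect at r = .5.
- **That entry at ISI ≥ 15 makes change scores relatively worse.** The cut lowers r, but it also lowers k. Starting from r = .5, k = 1 (variance ratio 1.00/.75 = 1.33), a cut at the baseline mean gave about r = .33, k = .66, a ratio of 1.12. The penalty shrank. The direction depends on correlations that the article does not give.
- **That every secondary outcome suffers the same loss.** Diary outcomes exist only at T0 and T1, so no omnibus problem arises. In Table 1, effort-reward imbalance and work engagement are taken only at T0, teacher self-efficacy only at T2 and user satisfaction only at T1.
- **That the test is the group main effect, diluted by the baseline score.** The article does not name that term as its test.

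**Conclusion.** The point holds as a mismatch between the sample size basis and the stated efficacy method. With three time points the interaction does not isolate T1, and that conclusion does not depend on r or k. With two time points the test is valid, and the issue is efficiency alone: the loss against ANCOVA runs from about 18 percentage points (k = 1, r = .3) to almost nothing (k = .6, r = .5). Whether power drops below 80% cannot be settled from the article, because r, k and the T2 effect are not given. The three-time figures also assume compound symmetry and k = 1, and all figures assume complete data. The stated N is correct for its own inputs. This should be corrected, but it does not invalidate the design.

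**What to change.** State one primary test: the difference between arms in ISI at T1, adjusted for T0 ISI. Use either an ANCOVA or a baseline-adjusted mixed model for T1 and T2 with the T1 contrast declared primary. Report the adjusted mean difference with its 95% confidence interval, and treat T2 ISI as secondary. Use the same baseline adjustment for sleep efficiency and total sleep time, where the only gain is efficiency, and for those secondary outcomes measured at T0 and again later.

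The cost is a change of wording. T0 ISI is already collected, no participants or visits are added, and N = 128 stays. With complete data and d = .50, power is then at least the planned 80% (83.7% at r = .3, 90.0% at r = .5). The adjusted difference can also be pooled directly if the planned imputation is multiple.

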#### Diary data

Sleep efficiency (SE) and total sleep time (TST) will be recorded in a sleep diary at pre- (T0) and post-treatment (T1), seven times in the course of seven days. We will compare SE and TST means in a repeated-measures ANOVA to evaluate treatment efficacy (see above). Diary data participants collect over the course of the intervention will be explored using multilevel modeling procedures.

#### Economic analyses

We will calculate direct and indirect costs and look at cost-effectiveness and cost-utility ratios to assess the economic impact of mental illness due to insomnia and occupational stress. A comparison will be made between the intervention and control groups on incremental costs and incremental effects. The incremental cost-effectiveness ratio (ICER) will be calculated as follows: ICER = (Δ costs/Δ effects) where Δ costs represents the difference in annual mean costs between intervention and control group, and Δ effects represents the difference in annual mean effects between the two groups. Bootstrapping with 5,000 iterations will be used to test the robustness of the ICER and quantify the uncertainty around the ratios, which will be plotted in a cost-effectiveness plane. The bootstrapped ICERs will also be presented in a cost-effective acceptability curve displaying the probability that the intervention is cost-effective for a wide range of willingness-to-pay ceilings. To test the robustness of the base-case findings, a multi-way sensitivity analysis will be performed. Several assumptions made in the base-case scenario (that is, concerning costs and volumes) will be changed to assess their impact on the ICER.

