### Procedure

Participants will be recruited during March to June 2013 through email distribution lists by the ministry of education in the German state of Nordrhein-Westfalen (NRW). Principals of primary, secondary and vocational schools are invited to circulate a flyer to their teaching staff. Interested teachers can apply for participation by an email to the primary study investigator (first author). The primary study investigator will provide interested teachers with a PDF containing additional detailed information and a request to complete an online screening questionnaire, which will be available on the same homepage that will contain all other study questionnaires and the online training. Teachers will obtain access to the homepage by using their email address and a self-chosen password. We will provide eligible participants with an ID number and then ask them to a) provide informed consent, b) complete baseline questionnaires (including a 7-day sleep diary) and c) participate in a diagnostic interview via telephone. The diagnostic interview will take about 20 minutes and include sections from the Structured Clinical Interview for DSM-IV (SKID-I)
[47] and the Structured Interview for Sleep Disorders (SIS-D)
[48]. The diagnostic interview will not be used as an inclusion or exclusion measure but will provide diagnostic data for primary insomnia, major depression and generalized anxiety disorder. After the diagnostic interview, participants will be randomized. Assessments will occur at baseline, before randomization (T0), eight weeks post-treatment (T1) and six months follow-up (T2). We chose eight weeks for T1 as a post-treatment measure to ensure that all participants will have completed the six week training. Figure 
1 illustrates an overview of the procedures the participants will undergo.

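### The ICER is defined from plain differences in group means with no baseline adjustment stated, although SF-6D utility and costs are both collected at T0

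*Protocol article*

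**What the plan says.** The Economic analyses section of the protocol article states that "A comparison will be made between the intervention and control groups on incremental costs and incremental effects". It then gives the ICER as Δ costs over Δ effects and defines each Δ as the between-group difference in annual means. Uncertainty is to be described by 5,000 bootstrap iterations, a cost-effectiveness plane and an acceptability curve. The sensitivity analysis is described as varying assumptions about costs and volumes. Baseline values appear in none of these steps.

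Under Economic evaluation, "QALYs will be obtained from the SF-6D". How the utilities are turned into QALYs is not described. In Table 1 (Instruments), the row that begins "Quality of life (SF-12" is marked at T0, T1 and T2. The TiC-P row is marked at T0 and T2 only.

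Under Randomization, "This random assignment is made in a 1:1 ratio", and no stratification or balancing factor is named. By contrast, the Treatment efficacy section analyses the clinical outcomes by repeated measures ANOVA, which uses T0. That method is not extended to costs or QALYs.

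**The concern.** A person's utility at T0 predicts utility at T1 and T2, and may enter the QALY itself. Past costs predict later costs. If the arms differ by chance at T0, a plain difference in means contains part of that difference. The bootstrap distribution is centred on the observed increments, so the imbalance also stays in the centre of the plane and in the acceptability curve.

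Cost-effectiveness is one of the trial's two stated hypotheses. The QALY difference over a short follow-up is likely to be a small denominator, where a modest shift matters. The baseline data that would remove most of this are already being collected.

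**Working it through.** **The plan's own figure.** Inputs from the Sample size section: "We expect a difference of Cohen’s d = .50" and "Given an alpha of .05 and 1 - beta = .80 in a two-tailed test". The two-sample t-test needs 63.77 per arm, rounded up to 64, with power 0.801 at 64. This reproduces "we will need 64 subjects in each condition with a total sample size of N = 128". That calculation serves the ISI; the article states no figure for the economic analysis.

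**Step 1: size of a chance baseline difference.** With 64 per arm, SE = SD × √(2/64) = 0.177 SD. The 95% range is ±1.96 × 0.177 = ±0.35 SD. The probability of a difference beyond 0.2 SD in either direction is 26%.

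**Step 2: carry-over into QALYs.** Assumptions, none given in the article: trapezoid area under the curve over weeks 0, 8 and 26; equal SD at each visit; the same correlation r between any two visits; utility SD 0.08–0.12; r = .3–.7; no loss of participants. The weights on mean utility are

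- T0: 4/26 = .154
- T1: (4 + 9)/26 = .500
- T2: 9/26 = .346

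The slope of mean utility on T0 utility is .154 + .846 r, which is .41, .58 and .75 for r = .3, .5 and .7. Carry-over is therefore partial; the direct share is 15%.

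The shift in six-month QALYs is slope × imbalance × 0.5 year:

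- Imbalance 0.2 SD, SD .08, r = .3: .408 × .2 × .08 × .5 = .003 QALY
- Imbalance 0.35 SD, SD .12, r = .7: .746 × .35 × .12 × .5 = .016 QALY
- Imbalance of one SE (0.177 SD), same two corners: .003 and .008 QALY

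For scale, an assumed utility gain of .03 at both T1 and T2 is worth .846 × .03 × .5 = .0127 QALY, so a one-SE imbalance is roughly 23–62% of it. If the gain were .06 (.0254 QALY), the same shift would be about 11–31%. Annualising doubles shift and gain alike and leaves these ratios unchanged.

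**Step 3: precision gained for QALYs.** Var(mean utility) = (1 − r) × Σw² + r in units of SD², with Σw² = .154² + .5² + .346² = .393. The variance remaining after adjustment is 1 − slope²/Var:

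| r | slope | Var | variance remaining | SE reduction |
|---|---|---|---|---|
| .3 | .408 | .575 | 71% | 16% |
| .5 | .577 | .697 | 52% | 28% |
| .7 | .746 | .818 | 32% | 43% |

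**Step 4: costs.** T0 costs are not part of follow-up costs, so they act only through r. An imbalance of 0.2–0.35 SD shifts the cost difference by r × imbalance, from .3 × .2 = .06 SD to .7 × .35 = .25 SD. The variance remaining is 1 − r²: 91%, 75% and 51% for r = .3, .5 and .7.

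**The case against.** The strongest objection is that the article condenses the economic analysis into one paragraph, and the model behind each increment may sit in a plan that is not shown. A reader might infer that the plan commits to a raw, unadjusted ICER. The text does not say that: it never calls the means unadjusted and does not exclude adjusted ones. This stands against that stronger reading. It does not remove the point, because the section does define both increments, fixes the bootstrap and describes the scope of the sensitivity analysis, and no baseline term appears in any of them.

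A reader might also infer that a baseline imbalance passes whole into the ICER. It does not. Carry-over is partial for QALYs and indirect for costs. The area under the curve is itself an assumption. If QALYs were built as change from baseline, the T0 coefficient would be .423 × (r − 1) years, a shift of opposite sign: about −.002 to −.004 QALY for a one-SE imbalance with r = .5–.7 and SD .10–.12. So neither the size nor the direction can be fixed from the document.

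Finally, a reader might infer bias or an invalid bootstrap. Under randomisation the imbalance is sampling error, and the bootstrap spread already includes it. On the assumptions in the working, the unadjusted SE of the QALY difference is .1341 × .08 × .5 = .005 to .1599 × .12 × .5 = .010. The one-SE shift of .003–.008 is a component of that SE, not an extra error. All of this stands. What remains is avoidable imprecision and a point estimate that keeps whatever imbalance occurred.

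**Conclusion.** The point holds as a missed improvement in the stated estimator, not as an error that biases the result. On its plain reading the ICER uses differences in means without baseline adjustment, although the needed T0 utility and cost data are collected. At 64 per arm the chance baseline difference has an SE of 0.177 SD, which follows from the sample size alone.

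Everything beyond that rests on assumed correlations, and the QALY amounts also on an assumed utility SD and QALY construction. For r = .3–.7, adjustment leaves about 71–32% of the variance of the QALY difference and about 91–51% of that of the cost difference. A claim that imbalance would halve the QALY gain cannot be drawn from the document, since it depends on an assumed true gain.

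The arithmetic covers QALYs and costs only; the effect measure for the cost-effectiveness ratio is not named in the section.

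**What to change.** State in the Economic analyses section that the QALY difference is the arm coefficient from a regression of QALYs on arm and T0 SF-6D utility, and that the cost difference is the arm coefficient from a regression of costs on arm and T0 TiC-P costs. Fit both regressions in each of the 5,000 bootstrap samples, resampling whole participants so that the cost–effect correlation is kept. Use the adjusted pairs for the ICER, the plane and the acceptability curve.

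With T0 utility as a covariate, the arm coefficient is the same whether QALYs are an area under the curve from T0 or that area minus T0 utility times the follow-up time, so the sign question raised above disappears.

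The cost is a few lines of analysis code and one or two sentences of text, with no new data and no change to N. Fixing it beforehand also removes a later choice between adjusted and unadjusted ICERs. If a fuller plan already specifies this, a sentence saying so is enough.
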